The secondary objective is to assess the effectiveness of the extended maintenance intervention compared to the control group on self-reported BMI in children 7–14 years old 1 year after the completion of health camp (secondary outcome). We hypothesize that children receiving the extended maintenance intervention will be more likely to maintain a healthier BMI compared to the control group.

The following research questions form the basis of the evaluation:

Process evaluation:

What are the characteristics of the children and families maintaining their results after 3 months and 1 year despite not receiving the extended maintenance intervention?What are facilitators and barriers in implementation of the extended maintenance intervention in the family and from intervention coordinators?What was the actual dose of intervention in the standard vs. the extended maintenance intervention and the association to the primary and secondary outcomes?

Effect evaluation:

Can an extended maintenance intervention after participating in a residential health camp maintain results on the primary outcome life satisfaction measured on the Cantril ladder and secondary outcome BMI 1 year after the completion of health camp (primary and secondary outcome) or at short-term follow-up (3 months after health camp)?Can an extended maintenance intervention after the residential health camp maintain results on intermediate outcomes: self-efficacy, self-esteem, social relations, health promoting behavior (food, exercise, sleep), school satisfaction, body satisfaction, and parental health promoting behavior, and parental self-efficacy after 3 months and 1 year.

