**Figure 4 F4:**
[figure not shown]
Flowchart of expected numbers of participants.

Historically it has been difficult to reach a satisfactory response rate for the long-term follow up questionnaires as mentioned before (27).

We used already collected questionnaire data from the camps to calculate the number of children needed to detect changes on the primary outcome (see Table 3). We made a random retrieval of 50 children from each of the five health camps, a total of 250.

Based on this calculation, we found a SD of 2.1. A prospective power calculation shows that with 80% power, we will be able detect a difference of 0.53 points on the Cantril ladder between groups with 144 in the intervention group and 894 in the control group. These power calculations are based on the assumptions that all the children complete the stay at the camp and all the children allocated to the extended maintenance intervention at the Liljeborg health camp, will accept this. If we assume there is a 8% drop out of all health camps, the calculation with 132 in the intervention group and 822 in the control group, we will be able to detect a difference of 0.55 on the Cantril ladder, making it a very small difference.

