### Data Analysis

We will use descriptive statistics to investigate baseline equivalence and loss to follow up. We will graphically visualize the development over time in both intervention group and control group 1 for the primary and secondary outcomes.

We will analyze the effectiveness of the extended maintenance intervention compared to control group 1 on the primary and secondary outcomes, using linear regression analysis and on explorative outcomes using logistic regression analyses. We will apply an intention-to-treat approach including all children in the intervention group they initially have been allocated to irrespective of whether they have completed the intervention or are lost to follow-up. Missing data will be replaced by multiple imputation. We will perform complete case analysis for sensitivity analyses.

The effect analyses will be adjusted for baseline factors including gender and age of the child, life satisfaction, BMI-*Z* score, and parental socioeconomic position.

For the total population at all five camps, we will calculate the standard deviation of the primary and secondary outcomes right after camp to calculate Cohen's *d* effect size.

Furthermore, we will perform sensitivity analysis restricted to the data from the Liljeborg health camp to identify any differences between camps (control group 2). We will investigate the association between intervention dose and effect (per protocol analyzes).

We will investigate if the effect differs by subgroups (see moderators in Figure 2).

We will summarize process measures using appropriate descriptive statistics including proportions, means (SD), and medians (IQR).

We will identify who is in most need of the intervention and find out who does not need the intervention.

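### The protocol promises to find out which children do not need the intervention, but the sample can reliably detect only a subgroup difference about twice its planned overall effect

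*Protocol article*

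**What the plan says.** Two sentences in the Data Analysis section of the protocol article matter here. The first announces an examination of effect modification: "We will investigate if the effect differs by subgroups (see moderators in Figure 2"). The second, placed after a sentence on summarising process measures, states a conclusion the study will reach: "We will identify who is in most need of the intervention and find out who does not need the intervention". It carries no qualification.

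The Sample Size Calculations section covers only the overall comparison. From existing camp questionnaires it reports: "Based on this calculation, we found a SD of 2.1". It continues that "A prospective power calculation shows that with 80% power" the study can detect 0.53 points "with 144 in the intervention group and 894 in the control group". With 8% leaving camp (132 and 822) the figure becomes 0.55. Nothing is said about the size of interaction that the study could detect.

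The research questions at the end of the Introduction include one, listed under process evaluation, that may also feed the second sentence: "What are the characteristics of the children and families maintaining their results after 3 months and 1 year despite not receiving the extended maintenance intervention".

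**The concern.** To say that a group of children does not need the extended intervention is to say that they would gain little or nothing from it over the standard one. That is a claim about the treatment effect within a group, and about how it differs from the effect in other groups. Such contrasts are estimated far less precisely than the overall effect for which the study is sized.

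If the protocol's own inputs leave the interaction poorly estimated, the promised conclusion will rest on noise, or on outcomes in control children that do not address benefit at all. The statement is not idle. The Ethical Issues section says the evaluation bears on the future of the extended intervention, and the process evaluation section looks ahead to scaling it up to other camps. A published statement that certain children do not need it could be used for targeting.

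**Working it through.** **Inputs.** SD 2.1, power 80%, group sizes 144/894 and 132/822, all from Sample Size Calculations. Assumption: two-sided 5%, since no level is stated.

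**1. Reproduce the protocol's figures.** Detectable difference = (1.960 + 0.842) × SD × √(1/n1 + 1/n2).
- 144/894: 2.802 × 2.1 × √(1/144 + 1/894) = 2.802 × 0.1886 = 0.528, against the stated 0.53.
- 132/822: 2.802 × 2.1 × √(1/132 + 1/822) = 2.802 × 0.1969 = 0.552, against the stated 0.55.

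A one-sided 5% level would give 0.47 and 0.49, so two-sided 5% is the level that fits.

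**2. Detectable interaction, two equal subgroups.** SE = SD × √(sum of 1/n over the four treatment-by-subgroup cells). With an even split this is exactly twice the overall SE.
- 144/894: SE = 2.1 × √(2/72 + 2/447) = 0.377; detectable interaction 2.802 × 0.377 = 1.06.
- 132/822: SE = 2.1 × √(2/66 + 2/411) = 0.394; detectable interaction 1.10.

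For scale, if the average effect is 0.53, an interaction of 1.06 means that one half gains nothing and the other gains 1.06, because (0 + 1.06)/2 = 0.53. Only a pattern that extreme is found with 80% power.

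**3. Power for an interaction as large as the planned overall effect.** Power = Φ(interaction/SE − 1.960).
- 144/894, interaction 0.53: Φ(1.405 − 1.960) = 29%.
- 132/822, interaction 0.55: Φ(1.397 − 1.960) = 29%.

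**4. What a non-significant half would show.** Within one half (72/447) the SE is 2.1 × √(1/72 + 1/447) = 0.267, so the 95% confidence interval is the estimate ± 0.52. An estimate of 0.20, for example, is non-significant, yet its interval runs from −0.32 to 0.72 and includes the full planned effect of 0.53.

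**5. Sensitivity.**

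| Variation | Detectable interaction | Power for an interaction equal to the overall target |
|---|---|---|
| 20/80 split, 144/894 | 1.32 | 20% |
| 20/80 split, 132/822 | 1.38 | 20% |
| Even split, 144/894, baseline adjustment with assumed correlation 0.3 to 0.5 | 1.01 to 0.92 | 31% to 37% |
| Even split, assumed 50% response at 1 year among 132/822 | 1.56 | not computed |

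The split of each moderator, the baseline correlation and the response rate are assumptions; the document gives none of them.

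**6. The route through control children.** Suppose the second sentence rests on the process question about children who maintain their results without the extended intervention. Those children show what happens under standard maintenance. Whether they would have done better still with the extended version requires comparison with similar children who received it, which is the treatment-by-moderator contrast of steps 2 to 4.

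**The case against.** Much can be said for the plan. The subgroup sentence is cautious, asks whether the effect differs, and points to moderators set down beforehand in the program theory. Low power for interactions is normal in a study sized for one primary hypothesis and is not in itself an error; the protocol never claims such power. The sentence about need stands apart from the subgroup sentence and may belong to the process evaluation. The Ethical Issues section ties the intervention's future to whether an effect is shown overall, and mentions no withdrawal by subgroup.

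Most of this stands. A reader might infer more: that subgroups will be tested at the full 5% level without multiplicity control, that a false subgroup difference is therefore likely, or that significance will be compared between strata. The document does not support these readings. It states no significance level. A multiplicity rule or an exploratory label may sit in an analysis plan that is not shown. The number of moderators is in Figure 2, which is also not shown, so no error rate can be fixed. No within-stratum testing is described.

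None of this rescues the unqualified sentence. An unseen analysis plan could add rules for testing, but it could not add the information that the promise requires. Reading the sentence through the process question replaces a poorly estimated effect contrast with a prognostic description, which does not answer the question of need.

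**Conclusion.** The concern holds for the one sentence that promises to establish who does and who does not need the intervention. On the protocol's own SD and group sizes, and assuming two-sided 5%, the detectable interaction for an even split is 1.06 to 1.10 points, twice the overall figure of 0.53 to 0.55. Power for an interaction as large as the overall target is about 29%. These figures assume that every child counted responds at 1 year, although the protocol itself reports that long-term response has been hard to obtain. Uneven splits make matters worse, and baseline adjustment helps only modestly.

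The primary analysis is not affected, and planning to look at moderators is reasonable. What the design cannot deliver is a firm statement that some children do not need the intervention.

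**What to change.** Keep the sentence announcing the moderator analysis. Replace the sentence on who needs the intervention with wording such as:

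> Effect modification by the moderators named in the program theory is exploratory. For each moderator we will report the treatment-by-moderator interaction on life satisfaction at 1 year with its 95% confidence interval. With an evenly split moderator and complete response, the study has 80% power only for an interaction of about 1.06 to 1.10 points. No subgroup will be described as not needing the intervention because its effect is non-significant or because its control children do well. Results will be used only to generate hypotheses for targeting.

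The process question on control children who maintain their results can stay, provided that its findings are presented as prognosis under standard maintenance.

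The cost is a few sentences and no new data. The downside is that the study gives up a firm statement on whom to target.

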### Protocol Amendment

All amendments to the protocol will be reported in the trial registration and be transparent in study papers.

We have already been obliged to introduce some amendments to the original trial registration due to the Covid-19 pandemic and modifications made by the intervention coordinators along the way. We originally planned to recruit children for a 52-week period but due to the fact that the Liljeborg camp initiated the online questionnaires faster than the other four health camps, we have extended the recruitment at Liljeborg camp with 10 weeks to obtain a larger intervention group. Furthermore, the covid-19 pandemic has influenced the recruitment period as the health camps have been locked down by the government twice during the year of recruitment along with shorter local lock downs due to outbreaks of covid-19 and periods of lower occupancy rates at the camps e.g., due to requirements from the government to have less people gathered in settings like this.

We originally planned to include objective measures of weight and height at baseline, post health camp and at the long-term follow-up at the Liljeborg health camp. However, due to the Covid-19 lockdown DCSH will not be able to gather all children at the Liljeborg health camp to participate in a reunion day 1 year after camp and obtain long-term objective measures of weight and height as originally planned. Instead, we must rely on self-reported measurements at all timepoints supplemented by findings on agreement between objective and self-reported measurements at baseline and post camp.

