## Methods and Analysis

### Study Setting

#### The Danish Christmas Seal Houses and the Health Camps—A Historical View

In Denmark there is a national focus on childhood overweight and obesity with several initiatives and interventions carried out mainly by volunteers or in municipality settings (23).

Since 1912, DCSH, a private charity foundation in Denmark, has offered sick or vulnerable children a stay at one of their camps. In the early years, focus was on children with tuberculosis, asthma, or other diseases. In the 1960s focus changed to children with overweight and in recent years there has been an increased focus on children with low life satisfaction and social and mental problems. DCSH has thereby adopted the WHO's broad definition of health and includes both physical, social, and mental health in their definition of health among children and adolescents.

DCSH currently runs five health camps in different parts of Denmark. The camps are called Fjordmark, Hobro, Skælskør, Kildemose, and Liljeborg and they offer stays for children from all municipalities in Denmark. The five camps can accommodate between 24 and 48 children at a time with a total of 990 children staying at one of the five camps per year. The children stay at the camp for 10 weeks but return to their homes on the weekends.

The camp accepts children of the age of seven to 14 years (see referral to camp below). Most participating children are between 11 and 14 years old. The distribution of gender is approximately 50/50 with a small overweight of girls. Approximately 5% of the children have a different ethnic background than Danish compared to 11% in the general population. More children attending the health camps have physical or mental problems compared to other children of the same gender and age (24). Compared to other children of the same age, a larger percentage of children attending a health camp live together with parents who have no education or job and/or are divorced or live apart (25). The children struggle with different problems such as low self-esteem, bullying, and/or low life satisfaction. A recent study reveals that 97% of children at the health camps have either overweight or obesity problems (24). Prior to the camp stay, approximately 73% of the children report having a low quality of life (24).

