#### Eligibility Criteria and Recruitment

##### Inclusion

All 7–14-year-olds who are signed up for a 10-week stay at one of the five health camps in the period from September 2019 to June 2021 will be enrolled in the effect evaluation. This also includes children who do not complete the health camp, according to the principle of intention to treat.

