### Sample Size Calculations

In total 1,038 children will attend the 10-week stay at one of the five camps during the recruitment period (see Figure 4). Approximately 288 will attend Liljeborg health camp and half (~144) will receive the extended maintenance intervention and the other half (~144) the standard maintenance intervention. The 750 children from the four other residential health camps are offered a standard maintenance intervention as well. We know from records at the health camps, that approximately 8% do not complete their stay at the camps. We do, however, have no knowledge of how many children turn down the offer of standard or extended maintenance.

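### Recruitment ran 10 weeks longer at Liljeborg only, across two lockdowns, yet the covariates named for the primary contrast include no entry period

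*Protocol article*

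**What the plan says.** All references are to the protocol article.

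- **Recruitment calendar (Protocol Amendment).** The starting plan was a single duration: "We originally planned to recruit children for a 52-week period". Because "the Liljeborg camp initiated the online questionnaires faster than the other four health camps", the authors report that "we have extended the recruitment at Liljeborg camp with 10 weeks to obtain a larger intervention group". The same section says "the health camps have been locked down by the government twice during the year of recruitment along with shorter local lock downs", and adds that occupancy was reduced at times.
- **Dates (Inclusion).** One overall window is given for all camps, "in the period from September 2019 to June 2021 will be enrolled in the effect evaluation", with no dates per camp.
- **Arms (Sampling and Allocation to Intervention Groups; Sample Size Calculations).** About 288 children attend Liljeborg. Home municipality, not time, splits them into about 144 on extended and 144 on standard maintenance. The other four camps supply 750 controls, making 894.
- **Analysis (Data Analysis).** The primary comparison is a linear regression of the intervention group against control group 1. "The effect analyses will be adjusted for baseline factors including gender and age of the child, life satisfaction", BMI Z-score and parental socioeconomic position. A sensitivity analysis restricted to Liljeborg (control group 2) is planned, and its stated purpose is to look for differences between camps.

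**The concern.** The primary outcome is life satisfaction one year after camp. Children who entered at different dates lived through different stretches of the pandemic during that year. If the arms differ in when their children entered, some of the difference between them may reflect the calendar and not the extended maintenance.

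The amendment creates such a difference. The extra weeks belong to Liljeborg alone, which supplies the whole intervention arm but only a minority of controls. None of the named covariates captures entry date. Baseline life satisfaction is measured before the camp stay, so it cannot carry information on what happened during the year after it. The Discussion's reassurance that the groups should be similar rests on the municipalities they come from and does not consider when the children entered.

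At stake is a bias in the primary estimate, in an unknown direction, which could mimic or mask part of an intervention effect.

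**Working it through.** **Inputs.** From Sample Size Calculations: SD 2.1, power 80%, 144 intervention children, 894 controls (144 Liljeborg plus 750 elsewhere), stated detectable difference 0.53, or 0.55 with 132 against 822. From Protocol Amendment: 52 weeks planned, plus 10 at Liljeborg, so 62 weeks there. Assumptions: two-sided alpha of 0.05 (not stated in the article), uniform intake over the 62 weeks, and calendars otherwise aligned.

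**1. The plan's own figures.** Detectable difference = (1.960 + 0.842) × SD × √(1/n1 + 1/n2).
- 144 against 894: 2.802 × 2.1 × √(1/144 + 1/894) = 0.528 (stated 0.53).
- 132 against 822: 0.552 (stated 0.55).

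Both reproduce.

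**2. Imbalance in entry period.**
- Intervention children entering in Liljeborg-only weeks: 10/62 = 16.1%.
- Controls entering in those weeks: (10/62) × (144/894) = 2.6%.
- Difference: 0.161 − 0.026 = 0.135.

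**3. Bias in the primary contrast.** Let the period effect be the mean difference in one-year life satisfaction between children entering in Liljeborg-only weeks and those entering in the common weeks. Then bias = 0.135 × period effect. The standard error is 2.1 × √(1/144 + 1/894) = 0.189, and the type I error is P(|Z + bias/0.189| > 1.96).

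| Assumed period effect (points) | Bias (points) | Two-sided type I error |
|---|---|---|
| 0.25 | 0.03 | 5.4% |
| 0.5 | 0.07 | 6.5% |
| 1 | 0.14 | 11% |
| 2 | 0.27 | 30% |

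The assumed effects have no source in the article; they only show the range. To create a spurious 0.53 from these weeks alone, the period effect would have to be 0.53/0.135 = 3.9 points. If the comparison used only the 750 controls from the other camps, the factor would be 0.161.

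**4. The planned Liljeborg-only contrast.** Both groups share one calendar, so the share entering in the extra weeks is 16.1% in each and the expected imbalance is 0. Its detectable difference is 2.802 × 2.1 × √(2/144) = 0.69, or 0.72 with 132 per group.

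**5. Price of restricting to common weeks.** Under uniform intake, 144 × 52/62 = 121 Liljeborg children remain per group, giving 121 against 750 + 121 = 871. The detectable difference is 2.802 × 2.1 × √(1/121 + 1/871) = 0.57.

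**The case against.** The strongest reply is that the plan already holds a comparison free of this imbalance. Within Liljeborg, children are split by municipality, so both groups meet the same closures and the same extra weeks. That analysis even handles closures specific to one camp, which a common calendar term would not. This stands as mitigation. It does not protect the primary estimate, because it is secondary, less precise (0.69 against 0.53) and framed as a check on camps. If it disagreed with the primary result, the plan gives no way to tell a period difference from a camp difference.

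A reader might also infer more than the article supports:

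- **That the model has no calendar term.** The covariate list is open-ended, in a condensed article whose analysis plan is not shown. The supportable statement is that none is named.
- **That a period effect falls wholly on the intervention arm.** The extension covers the whole camp and adds Liljeborg controls too, so only about 0.135 of the effect reaches the contrast.
- **That the earlier start adds to the 10 weeks.** The article gives the earlier start as the reason for the extension and gives no dates per camp. They may be the same weeks and should not be counted twice.
- **That the planned sample size is wrong.** The article says "In total 1,038 children will attend the 10-week stay at one of the five camps during the recruitment period", and elsewhere gives "a total of 990 children staying at one of the five camps per year". One may note that 1,038 = 990 + 48 and suspect that normal occupancy was assumed, or set the 52 weeks against the longer window under Inclusion. But no derivation of 1,038 is given, no shortfall is quantified, the 52 weeks is described as the original plan, and the detectable differences follow from their inputs. No error in the sample size is shown.

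**Conclusion.** The point holds in limited form. The amendment associates entry period with arm in the primary contrast, and the covariates the article names do not address it. Under uniform intake over 62 weeks, about 0.135 of any period effect enters the estimate. An effect of 0.5 points would matter little; 1 point would give a bias of about a quarter of the stated detectable difference (0.135/0.53 = 0.26) and roughly double the type I error. Neither the size nor the direction of a period effect can be derived from the article, and camp-specific closures could make the imbalance larger or smaller. This is a weakness that should be repaired because the repair is cheap. It does not show that the primary result will be misleading.

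**What to change.** 1. Add calendar time of camp start, for example intake quarter, to the pre-specified covariates of the primary model. Liljeborg controls also entered in the extra weeks, so the term and the intervention effect can both be estimated.
2. Add a sensitivity analysis restricted to intake weeks in which all five camps were enrolling. This requires the actual enrolment dates of each camp.
3. State that the Liljeborg-only analysis also serves as the check on period effects, including closures specific to a camp.

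The cost is a few degrees of freedom in the primary model and some loss of sample in the restricted analysis, whose detectable difference would be about 0.57 under the assumptions above. The changes need camp start dates but no new data from children or parents.

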**Secondary outcomes**					
Weight and height (BMI) Objective measures	*What is your weight (in kg)?*	HBSC	All children	Objective measures from the health camps at baseline and post health camp	Kg
	*What is your height without shoes (in cm)?*	HBSC	All children	Objective measures from the health camps at baseline and post health camp	Cm
Weight and height (BMI) Self-reported	*What is your weight (in kg)?*	HBSC	All children	– Baseline – Post health camp – Short-term follow up **– Long-term follow up**	Kg
	*What is your height without shoes (in cm)?*	HBSC	All children	– Baseline – Post health camp – Short-term follow up **– Long-term follow up**	Cm

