**Process evaluation measures**					
Implemen-tation measures	*Context, reach, dose delivered and received, fidelity/adaption, appreciation, and contamination*	Developed for study	Children + parents	– Baseline – Extra questionnaire – Short-term follow up	
	*Context, reach, dose delivered and received, fidelity/adaption, appreciation, and contamination*	Developed for study	Intervention coordinators	Start, mid, end intervention questionnaires	

The primary outcome is children's life satisfaction 1 year after completion of camp (long-term follow up), and will be measured in the child questionnaire by an adapted version of the Cantril ladder used in the HBSC study questionnaire (44). The outcome will be measured at all four time points.

The secondary outcome is self-reported BMI 1 year after completion of camp (long-term follow up). It will be measured objectively twice at the five health camps by the personnel on their scale at the beginning and end of the 10-week health camp (baseline, post health camp) and self-reported by the child in the questionnaires at all four time points.

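### Self-report is extended to all time points although staff-measured height and weight remain available at baseline; the source of the baseline BMI-Z covariate should be named, and the BMI model should use both measures

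*Protocol article*

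**What the plan says.** The Protocol Amendment section explains that the reunion day at Liljeborg, where height and weight were to be measured 1 year after camp, cannot take place. It concludes that "we must rely on self-reported measurements at all timepoints", "supplemented by findings on agreement between objective and self-reported measurements at baseline and post camp".

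Measured values still exist earlier in the study. The Outcomes section says of BMI: "It will be measured objectively twice at the five health camps by the personnel on their scale at the beginning and end" of the stay. Table 3 lists these values among the secondary outcomes as "Objective measures from the health camps at baseline and post health camp". The secondary outcome itself is the self-reported value at 1 year.

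The Data Analysis section states: "The effect analyses will be adjusted for baseline factors including gender and age of the child, life satisfaction, BMI-*Z* score" and parental socioeconomic position. It does not say which baseline BMI-Z is meant. It also plans multiple imputation, without naming the variables in the imputation model.

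The Discussion places the self-report limitation at 3 months and 1 year only. It gives the paired measured and self-reported values one use: exploring whether disagreement between them is similar in the two groups.

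**The concern.** The amendment's conclusion is wider than its cause. Losing the 1-year measurement forces self-report at 1 year. It does not force self-report at baseline or post camp, where staff measure every attending child. The sentence also sits badly with the Discussion, which treats self-report as a limitation of the two follow-ups only.

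The choice of baseline measure matters because the Sampling and Allocation section assigns children by home municipality, and the Discussion accepts a risk of selection bias. Covariate adjustment is the stated remedy. If the covariate carries random reporting error, its regression slope is attenuated, and part of any true baseline BMI difference stays in the estimated effect on BMI. The respondents are aged 7 to 14, and in the pilot the youngest had trouble reading some items, so some reporting error is to be expected. A second, staff-measured value is already collected and has no stated role in the effect model.

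**Working it through.** **Plan's own figure.** The article gives no power or precision figure for BMI. Its detectable differences (0.53 and 0.55) concern the Cantril ladder and have no bearing here.

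**Inputs.** From the documents: self-reported outcome at 1 year, linear regression with a baseline BMI-Z covariate, group sizes 144 and 894. Assumed, because the documents give none of them: true BMI-Z variance V_T = 0.49 (SD 0.7) at both times; correlation ρ = 0.85 between true baseline and true 1-year values; true baseline group difference D = 0.2; no treatment effect; variance V_b of a child's persistent reporting bias, unrelated to group; variance V_e of occasion error; measured-value error SD 0.05 (V_m = 0.0025).

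**Model.** Self-report = true value + persistent bias + occasion error. The persistent bias is shared by baseline and 1 year. Then V_S = V_T + V_b + V_e.

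**Self-report alone.** The slope is (ρV_T + V_b)/V_S. The part of the baseline difference left in the effect is D × (ρ − slope). Residual variance is V_S − (ρV_T + V_b)²/V_S.

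**Both measures.** The coefficients (β_O, β_S) solve the two normal equations with covariance matrix [[V_T + V_m, V_T], [V_T, V_S]] and right-hand side (ρV_T, ρV_T + V_b). The part left is D × (ρ − β_O − β_S).

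**Middle case in full** (bias SD 0.20, occasion SD 0.25):
- V_S = 0.49 + 0.04 + 0.0625 = 0.5925.
- Slope = (0.4165 + 0.04)/0.5925 = 0.7705.
- Left over = 0.2 × (0.85 − 0.7705) = 0.016.
- Residual SD = √(0.5925 − 0.4565²/0.5925) = 0.491.
- With both: β_O = 0.447, β_S = 0.401; left over 0.0005; residual SD 0.473.

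| Bias SD / occasion SD | Left over, self only | Share of 0.2 | Left over, both | Residual SD: self / measured / both | Fall, self to both |
|---|---|---|---|---|---|
| 0.15 / 0.15 | 0.006 | 3% | 0.0003 | 0.418 / 0.428 / 0.412 | 1.4% |
| 0.20 / 0.25 | 0.016 | 8% | 0.0005 | 0.491 / 0.490 / 0.473 | 3.7% |
| 0.25 / 0.40 | 0.036 | 18% | 0.0006 | 0.625 / 0.600 / 0.585 | 6.4% |

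Two boundary cases:
- **No persistent bias** (0 / 0.25): self-report alone leaves 0.019, and residual SD falls from 0.488 to 0.447 with both.
- **Strong persistent bias** (0.40 / 0.15): self-report alone leaves about −0.001. Residual SD is 0.422 with self-report, 0.566 with the measured value alone, and 0.422 with both.

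**Against sampling error.** With 144 and 894 children and complete follow-up, SE ≈ residual SD × √(1/144 + 1/894) = residual SD × 0.0898. This gives 0.038, 0.044 and 0.056 in the three main cases. The leftover bias is then about 0.16, 0.36 and 0.63 of a standard error.

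**The case against.** The strongest reply is that a self-reported baseline is a defensible partner for a self-reported outcome. It keeps one instrument throughout and absorbs each child's reporting habit. This stands against replacing one measure with the other: the measured value alone gives a larger residual SD in the first row of the table and a much larger one in the strong-bias case. It does not stand against using both, which has the lowest or equal-lowest residual SD in every case.

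The second reply is that the error sizes and the imbalance are assumed, the Discussion expects no large systematic differences, and the first two questionnaires are completed at camp with staff help encouraged. That is fair. It keeps the point modest and may put the real figure near the low end.

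The third is that the source of a covariate is analysis-plan detail. Silence alone would be no finding. But the amendment states a choice for every time point, that choice does not follow from the reason given, and the Discussion describes the limitation differently.

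A reader might go further in three ways that the documents do not support:
- **That the measured values are kept solely for an agreement check.** The text does not say solely, and Table 3 still lists them under secondary outcomes.
- **That the imputation leaves them out.** No imputation variables are named, so exclusion is not stated.
- **That the error leaks into the primary life-satisfaction model.** That model uses the same covariate, but no size for such leakage has been shown, and it would have to act on the ladder after adjustment for baseline life satisfaction.

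**Conclusion.** The point holds as a wording inconsistency with a modest analytic consequence for the secondary outcome. Self-report is extended to time points where measured values exist, and the baseline BMI-Z covariate has no named source. If it is the self-reported value, as the amendment suggests, a true baseline difference of 0.2 BMI-Z would leave about 0.006 to 0.036 BMI-Z (3% to 18%) in the effect estimate. With both measures it would leave less than 0.001, and residual SD would fall by about 1% to 6% (0% to 8% if the two boundary cases are counted).

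These figures rest on the assumed BMI-Z SD, correlation, error sizes and imbalance, and on reporting bias being unrelated to group. The bias scales in proportion to the imbalance and vanishes if there is none. Nothing here shows a problem with the primary analysis.

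**What to change.** 1. In Protocol Amendment, limit the self-report sentence to the BMI outcome and its trajectory over time, and make it agree with the Discussion on where self-report is a limitation.
2. In Data Analysis, name the source of baseline BMI-Z. Adjust the BMI model for measured and self-reported baseline BMI-Z together. Do not swap one for the other, because self-report carries the child's persistent reporting bias.
3. As a sensible addition, state that measured baseline and post-camp BMI-Z enter the imputation model as auxiliary variables. Keep the post-camp value out of the main effect model, because both maintenance programmes begin during the stay.

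The cost is a few sentences and one extra covariate. No new data are needed, since all five camps already take the measurements.
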